### Statistical methods

We will follow an intention-to-treat (ITT) approach. To estimate the potential impact of the intervention on the risk of dengue seroconversion, we propose a conditional (multilevel) modeling approach (i.e., using mixed effects models) [69]. To estimate the incidence risk ratio of seroconversion in the intervention group relative to the control group, a log-binomial model will be used which assumes a log link under the assumption of a binomial distribution [70]. Since the intervention effect of marginal and conditional models are only the same for the identity and log links [69], if convergence is an issue, a robust Poisson model with log link and robust variance will be used [70]. In addition to the fixed effect for the intervention, the log-binomial mixed model will have random effects for strata, measurement period (baseline, first follow-up, second follow-up), household, and census tract (cluster). The random effects for period will allow us to assess period by period differences in the risk of seroconversion. Also, as an alternative to the strata random effects, we will consider the baseline risk indicator (cumulative dengue incidence at the bairro level) that was used to stratify clusters. Additional baseline covariates may be considered for inclusion at the patient and household level (e.g., age, sex, socioeconomic status). We anticipate that the cluster sizes will remain relatively similar across all clusters but if losses due to attrition result in significant differences, we will then use inverse probability weights by cluster size in the analysis. For the primary outcomes of adult female *Aedes* density, we will use the same approach: a conditional (multilevel) modeling approach (i.e., using mixed effects models) with a Poisson distribution. For KAP and social capital, they will be examined as potential effect modifiers/confounders with each outcome. An index of KAP will be created using principal component analysis. Additionally, indicators on the community interventions captured from the fidelity analysis (e.g., content, coverage, frequency, and duration) may be included as fixed effects in the models to estimate the impact of intervention variability on the results.

Data will be analyzed descriptively immediately after the baseline survey to disseminate the results during the needs assessment. Following this, the data will be analyzed every 6 months for preliminary results with a global analysis at the end of follow-up. The qualitative research analyses obtained from community focus groups and interviews will occur after endline.

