### Trial design

We will follow a parallel pragmatic cluster randomized controlled trial (cRCT) design with randomization at the census tract level with equal allocation to the two arms, to evaluate the effectiveness of community mobilization measured by the risk of primary DENV infection, self-reported dengue cases, and *Aedes* infestation rates. The quantitative baseline assessment will include a household questionnaire, entomological evaluation of households and high-risk communal areas, and blood samples (from finger pricks) from children aged 3–9 years. Following the baseline assessment, allocation will occur after which community mobilization activities will begin for a period of 24 months. Baseline community interviews and focus groups for the qualitative studies will be performed just after allocation.

This is an investigator-initiated trial that was registered with ISRCTN66131315 prior to enrollment. The trial protocol was developed according to the Standardized Protocol Items: Recommendations for Interventional Trials (SPIRIT) guidelines (Additional file 1) [35].

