#### Allocation

After both baseline collections, the rate of IgG seroconversion of each cluster will be calculated. Based on the overall distribution of seroconversion rate, there will be five risk strata created and each cluster from the baseline assessment will then be assigned to a risk stratum. A computer generated (block) randomization of each enumerated member of the strata will be assigned to either the intervention or control arm.

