#### Additional and subgroup analyses

Given the potential for participants to have more than one dengue infection during the study period, the rate of dengue infection will be modelled using Poisson regression, while using random effects strata, measurement period (baseline, first follow-up, second follow-up), household, and census tract (cluster). Additional baseline covariates may be considered for inclusion at the patient and household level (e.g., age, sex, socioeconomic status).

We will assess any differences in the associations of intervention and risk of dengue seroconversion by age group (≤ 5 yrs. and ≥ 6 yrs) and by socio-economic status (SES). Separately for the age group and SES variables, we will conduct a Cochran Q test [71] to test for differential changes in risk across time points between the vulnerable and non-vulnerable subgroups. Then, we will extend the models to allow for differential effects by including interaction terms between the intervention variable and a dummy variable for the vulnerable subgroup of interest [72]. We will finally consider an Oaxaca-Blinder decomposition analyses [73] to decompose the treatment effect variable between subgroups and estimate the exact contribution of the intervention to changes in inequities occurring after the implementation of the intervention. These are secondary objectives and the study may not be sufficiently powered to detect important differences between these subgroups for one or both variables.

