#### Spatial analyses

Spatial analyses will be carried out to study the extent to which cases of dengue are spatially differentiated, and assess predictors that could explain these differences. We will use local methods of aggregates detection in space. The spatial scan approach elaborated by Kulldorf [74] will be adapted for our purpose. Typically, the scan statistic is used to identify unusual clustering of cases, but we will capitalize on its properties to determine whether any observed spatial heterogeneity is due to a few distant spatial units or to larger geographic zones of varying risk [75]. Geographically weighted regressions [76] will enable understanding the relation between the outcomes of primary interest: IgG seroconversion and adult female *Aedes* density, while cluster analysis using Local Indicators of Spatial Association [77] will allow us to assess of the significant of spatially-concentrated cases. We will examine various environmental and population-level demographic spatial predictors that could explain the spatial heterogeneity of dengue transmission risk using a Bayesian hierarchical Poisson model.

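### With baseline as a modelled period and no tract-by-period random effect, the intervention term has either too small a standard error or a diluted effect, depending on a coding the protocol does not state

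*Protocol article*

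**What the plan says.** Under Statistical methods, the seroconversion model is given by its terms: "In addition to the fixed effect for the intervention, the log-binomial mixed model will have random effects for strata", and the full list reads "random effects for strata, measurement period (baseline, first follow-up, second follow-up), household, and census tract (cluster"). The three periods are named, and baseline is one of them. The period effects have a stated purpose: "The random effects for period will allow us to assess period by period differences in the risk of seroconversion". The second primary outcome follows suit: "For the primary outcomes of adult female *Aedes* density, we will use the same approach". The Poisson model for repeat infections, under Additional and subgroup analyses, has the same list: "while using random effects strata, measurement period (baseline, first follow-up, second follow-up), household, and census tract (cluster"). None of these places names a tract-by-period term. Robust variance appears only as a fallback if the log-binomial model fails to converge, and its clustering level is not given.

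Baseline is unexposed in both arms. Trial design states: "Following the baseline assessment, allocation will occur after which community mobilization activities will begin for a period of 24 months". Participant timeline places an entomological survey at baseline and yearly ones after it. For seroconversion, Allocation says "After both baseline collections, the rate of IgG seroconversion of each cluster will be calculated", whereas Outcomes defines the event as a change to positive at follow-up.

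The protocol does not say what value the intervention variable takes in the baseline period.

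**The concern.** The listed terms allow a tract to be high or low in all periods alike, and a period to be high or low in all tracts alike. They do not allow one tract to have a bad season that its neighbours miss.

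Once baseline is an outcome period and the intervention switches on after it, the effect is estimated largely from change within tracts. Tract-specific seasonal variation is the relevant error for that change, and the model has no component for it. It falls into the residual, where it is averaged over all the children in a tract and almost disappears from the standard error. Intervals are then too narrow and false positive findings too frequent. Comparisons between periods are affected in the same way.

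The other coding, arm membership held constant over all three periods, avoids this but counts a period without intervention as if it were treated.

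**Working it through.** **The plan's own figure.** Inputs from Sample size: risks 0.30 and 0.2115, ICC 0.07, 60 per cluster, 80% power, 5% significance (taken as two-sided). Children per arm without clustering: (1.960 + 0.842)² × (0.30×0.70 + 0.2115×0.7885) / 0.0885² = 377.6. Design effect: 1 + 59×0.07 = 5.13. Clusters per arm: 377.6 × 5.13 / 60 = 32.3. With 32 clusters, power is 0.797. The stated 32 is reproduced. It is a single two-arm comparison and is not affected by this point.

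**Set-up.** K = 34 tracts per arm, m = 60 per tract and period, three periods, linear scale, period fixed, household and strata effects left out. Total variance 0.30×0.70 = 0.21. Between-tract variance 0.07×0.21 = 0.0147; within-tract variance 0.1953, so e = 0.1953/60 = 0.003255. Let ρ be the share of between-tract variance that persists from one period to the next. It is not in the protocol and is an assumption. Stable part u = 0.0147ρ; tract-by-period part c = 0.0147(1−ρ).

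**What the planned model fits.** Without a tract-by-period term:
- residual s² = 0.1953 + (2/3)c×(180/179), and e′ = s²/60
- tract variance τ² = u + c/3 + e/3 − s²/180
- weight on the baseline β = τ²/(τ² + e′)

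**Intervention coded 0 at baseline, 1 after.** The estimator is the arm difference in (follow-up mean − β × baseline).
- Model variance = (2/K)[τ²(1−β) + e′/2]
- True variance = (2/K)[(u + c/2 + e/2) + β²(u + c + e) − 2βu]

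At ρ = 0.7: u = 0.01029, c = 0.00441, s² = 0.19826, e′ = 0.003304, τ² = 0.01174, β = 0.780.
- Model SE = √[(2/34)(0.002579 + 0.001652)] = 0.0158
- True SE = √[(2/34)(0.014123 + 0.010935 − 0.016061)] = 0.0230
- Ratio 0.69; type I error = 2[1 − Φ(1.96×0.686)] = 0.179

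| ρ | Model SE | True SE | Ratio | Type I error | SE with tract-by-period term |
|---|---|---|---|---|---|
| 1.0 | 0.0159 | 0.0159 | 1.00 | 5.0% | 0.0159 |
| 0.9 | 0.0159 | 0.0187 | 0.85 | 9.6% | 0.0185 |
| 0.7 | 0.0158 | 0.0230 | 0.69 | 17.9% | 0.0220 |
| 0.5 | 0.0156 | 0.0262 | 0.60 | 24.2% | 0.0238 |

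The last column is √{(2/K)[(u + c/2 + e/2) − u²/(u + c + e)]}.

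A simulation of the log-binomial mixed model under no effect (300 runs per setting) gave 6.7%, 16.7% and 28.3% at ρ = 1.0, 0.8 and 0.5.

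**Constant arm indicator.** Model and true variance are both (2/K)(u + c/3 + e/3), because τ² + s²/180 equals that bracket. The ratio is 1.00 at every ρ. The coefficient, however, averages over an unexposed period: (0 + 0.0885 + 0.0885)/3 = 0.059. The SE is 0.0295, 0.0275 and 0.0253 at ρ = 0.9, 0.7 and 0.5, so power Φ(0.059/SE − 1.96) is about 52%, 57% and 65%.

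**Sensitivity.** Only IgG-negative children can seroconvert, so fewer than 60 may be at risk. With an assumed 30 (e = 0.1953/30 = 0.00651, 90 in place of 180, 89 in place of 179), the same formulas give 7%, 11% and 14% at ρ = 0.9, 0.7 and 0.5. Simulations that also allocate within five baseline strata gave about 8%, 12% and 12% with 30 at risk, and 12%, 14% and 22% with 60.

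**The case against.** The strongest reply is that the inflation depends on a coding that the protocol does not state. Statistical methods describes a risk ratio between the two groups, and Sample size plans a plain two-arm comparison; both read naturally as a constant arm contrast. This stands. A reader might infer that the intervention standard error is too small as the plan is written, and the document does not support so general a claim. But the arm reading does not rescue the model, because with baseline included it dilutes the effect.

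Second, a baseline seroconversion outcome may not exist. If only the two follow-up periods carry outcomes, the arm term is constant over exposed periods. A simulation of that case (400 runs per setting, no tract-by-period term) gave 5.0%, 4.3% and 6.5% at ρ = 0.9, 0.7 and 0.5. This stands for seroconversion, since Outcomes and Allocation point in different directions. It does not help *Aedes* density, which is measured at baseline.

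Third, the size rests on an assumed ρ, and lower at-risk numbers and stratified allocation reduce it. This also stands: in the checks above the inflation shrank but did not vanish. The Spatial analyses section, which aims to "study the extent to which cases of dengue are spatially differentiated", concerns differences between places. It should not be read as evidence that those differences change from season to season.

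Fourth, an article condenses, and a fuller plan might nest period within tract. That is possible, but the model is stated by named terms, with period and tract listed separately and period effects described only as differences between periods. One clause would settle it.

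**Conclusion.** The point holds in conditional form. With baseline as a modelled outcome period, the listed random effects give a sound analysis only if tract risk is perfectly stable between periods and the intervention is coded 0 at baseline. With that coding and less than perfect stability, the standard error is about 15% to 40% too small for ρ between 0.9 and 0.5, and type I error is about 10% to 24%. These figures assume 60 at risk per tract and period, ICC 0.07, a linear scale and no household or strata effects; fewer at risk or stratified allocation brings them down. With a constant arm term the test keeps its level, but the effect loses about one third.

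The point applies clearly to *Aedes* density. The sizes above were computed for a seroconversion-type outcome, and none is claimed for mosquito counts. For seroconversion the point applies if a baseline outcome enters the model. It should be settled before the outcome analysis, but it does not call the sample size into question.

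**What to change.** State that the intervention variable is 0 in both arms at baseline and 1 in intervention tracts after allocation. Add a census-tract-by-period random intercept to the models for both primary outcomes and to the Poisson model for repeat infections.

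Alternatively, model only the two follow-up periods, with the tract's baseline value as a covariate and robust variance clustered on tract. In either case, say whether a baseline seroconversion outcome exists, so that Outcomes and Allocation agree.

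The cost is one more variance component and somewhat wider intervals when tract-season variation is real. In the approximation above, the reported SE goes from 0.0158 to 0.0220 at ρ = 0.7, still small against the planned difference of 0.0885. No new data are needed.

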#### Participant timeline

Household visits for the questionnaire will occur at dry season and rainy season baseline and at endline (Figs. 1 and 2). The seroprevalence baseline and follow-up surveys will occur yearly (for 3 years), 5 months after the rainy season peak to allow the maximum levels of IgG to be reached without residues of other immune reactions to cross-react [50]. A baseline entomological survey will occur in rainy season, the same period as the household questionnaire. Following baseline, entomological surveys will occur yearly during the rainy season. Community focus groups and interviews will occur twice a year, starting with the baseline assessment.

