#### Sample size

Our pilot data, along with a research member’s (NA) RCT in Mexico and Nicaragua facilitated the sample size estimation. Our primary outcome of interest is risk of dengue seroconversion in 3 to 9 years old. The local pilot study’s intraclass correlation coefficient (ICC) was 0.08 across the 10 control clusters and the control group risk of seroconversion was approximately 0.30 (population 5–15 years old). The community mobilization RCT for dengue prevention by Andersson et al. [7] determined an ICC of 0.03 across 150 clusters for dengue seroconversion in children aged 3 to 9 and a relative risk reduction of 29.5% (95% CI 3.8 to 55.4). Using the approach of Reich et al. [51] for finding sample sizes to compare proportions between group, assuming a risk of seroconversion of 0.30 in the control group and 0.2115 in the intervention group (based on relative risk reduction of 29.5%) and an ICC of 0.07, for 80% power, a significance level of 0.05 and 60 individuals per cluster, 32 clusters are required in each arm. An additional two clusters per arm will be added, in the event that a cluster is removed from the study due to violence creating unsafe conditions for field staff [37, 52]. To have a sufficiently powered analysis in the case of a 30% attrition rate of participants, 60/0.7 = 86 individuals per cluster per arm are required. There will be a total of 5848 participants recruited for this study (86 individuals/cluster × 68 clusters).

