**Fig. 3 Fig3:**
[figure not shown]
Map of Fortaleza

Each census tract or cluster will be enumerated and the cluster eligibility criteria will be applied. Following the identification of eligible clusters, a proportionate stratified random sample of eligible clusters will be conducted. The stratification will be based on a dengue risk index calculated from the cumulative incidence of dengue notifications from 2016 to 2018 per neighbourhood or bairro, available from the Fortaleza Municipal Health Secretariat [57]. Census tracts within each bairro will be assigned to the same risk strata. Furthermore, a 400 m buffer for each cluster will be used to reduce contamination, creating a 800 m minimum distance between clusters. Clusters within that boundary area will be replaced by the next cluster, from a ranked list based upon stratification criteria [58].

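### The primary model may swap the five strata used to randomise clusters for bairro dengue incidence, which was used only to sample them

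*Protocol article*

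**What the plan says.** The protocol article describes two stratifications.

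- **Sampling (Cluster selection).** Eligible census tracts are drawn by proportionate stratified sampling: "The stratification will be based on a dengue risk index calculated from the cumulative incidence of dengue notifications from 2016 to 2018". The index is computed per bairro, and all tracts in a bairro fall in the same stratum.
- **Randomisation (Allocation).** After the baseline collections, a serological rate is calculated for each cluster: "Based on the overall distribution of seroconversion rate, there will be five risk strata created". Clusters are block-randomised to the two arms within those strata.

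Statistical methods gives the primary log-binomial mixed model random effects for strata, period, household and census tract, without saying which strata are meant. It then says: "as an alternative to the strata random effects, we will consider the baseline risk indicator (cumulative dengue incidence at the bairro level"), and identifies this indicator as the one by which clusters were stratified. No rule is given for choosing between the two. The *Aedes* density outcome is to be modelled in the same way.

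**The concern.** The alternative term belongs to the sampling design, not to the randomisation. Bairro incidence takes one value for all tracts in a bairro and cannot reproduce five strata built from each cluster's own serology.

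Stratified randomisation removes between-stratum variance from the treatment contrast. If the model leaves out the strata, and nothing else in it carries their information, that variance stays in the estimated residual cluster variance. The reported standard error is then larger than the true one. Intervals are too wide, the test rejects too rarely under the null, and precision gained by the design is not used.

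A wording problem in Allocation bears on the same strata. Under Outcomes, seroconversion is a change from negative to positive at follow-up, which needs two samples. Participant timeline says "The seroprevalence baseline and follow-up surveys will occur yearly (for 3 years), 5 months after the rainy season peak". Allocation does not say which samples give a seroconversion rate before allocation.

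**Working it through.** **Inputs (Sample size section).** "assuming a risk of seroconversion of 0.30 in the control group and 0.2115 in the intervention group"; ICC 0.07; "for 80% power, a significance level of 0.05" (two-sided assumed); "60 individuals per cluster, 32 clusters are required in each arm"; "An additional two clusters per arm will be added", giving 34 per arm and 68 in all.

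**1. The plan's own figure.** Design effect = 1 + 59 × 0.07 = 5.13. Variance sum = 0.30 × 0.70 + 0.2115 × 0.7885 = 0.3768. Individuals per arm before clustering = 0.3768 × (1.96 + 0.8416)² / 0.0885² = 377.6. Clusters per arm = 377.6 × 5.13 / 60 = 32.3. With 32 clusters, power is 79.7%. The stated 32 is reproduced, with no credit taken for stratification. With 34 clusters, SE = √(0.3768 × 5.13 / 2040) = 0.0308 and power = Φ(0.0885/0.0308 − 1.96) = 82.0%.

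**2. Effect of dropping the strata.** The between-cluster share of the variance of a cluster mean is f = 0.07 × 60 / 5.13 = 0.819. Let R² be the share of between-cluster variance that the strata explain, and c the fraction of that information carried by bairro incidence. Neither is in the documents; both are assumptions.

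- True SE = 0.0308 × √(1 − f·R²)
- Model SE with bairro incidence instead of strata = 0.0308 × √(1 − f·R²·c)
- Actual alpha = 2 × [1 − Φ(1.96 × model SE / true SE)]
- Power = Φ[(0.0885 − 1.96 × model SE) / true SE]

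Results for 34 clusters per arm:

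| R² | c | SE ratio | Actual alpha | Power, bairro instead | Power, strata kept |
|---|---|---|---|---|---|
| 0 | any | 1.00 | 0.050 | 82.0% | 82.0% |
| 0.1 | 0 | 1.04 | 0.041 | 83.0% | 85.1% |
| 0.2 | 0 | 1.09 | 0.032 | 84.2% | 88.2% |
| 0.2 | 0.5 | 1.05 | 0.040 | 86.2% | 88.2% |
| 0.4 | 0 | 1.22 | 0.017 | 86.8% | 93.9% |
| 0.4 | 0.5 | 1.12 | 0.029 | 90.7% | 93.9% |
| 0.5 | 0 | 1.30 | 0.011 | 88.3% | 96.3% |
| 0.5 | 0.5 | 1.16 | 0.023 | 92.9% | 96.3% |
| any | 1 | 1.00 | 0.050 | as strata kept | as left |

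**3. Simulation with a bairro covariate.** Cluster-level linear model, 68 clusters, five strata, 6,000 trials per cell. The shares of between-cluster variance explained and the correlations are assumed.

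| Baseline serology explains | Bairro incidence explains | Correlation | Power, bairro instead | Power, strata kept |
|---|---|---|---|---|
| 10% | 10% | 0.3 | 84.2% | 84.0% |
| 25% | 15% | 0.4 | 86.2% | 88.1% |
| 25% | 25% | 0.5 | 88.8% | 88.0% |
| 50% | 25% | 0.5 | 89.9% (alpha 2.7%) | 93.8% |

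Where bairro incidence was only weakly related to baseline serology (correlation 0.3) and had no prognostic value of its own, the swap gave about 83% against 88% at 25% explained, and 85% against 94% at 50%. Over all scenarios examined the cost ran from 0 to about 10 points, and from 0 to 8 where bairro incidence was itself prognostic. Strata plus bairro incidence was at least about as good as either alone.

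**The case against.** The default model already contains strata; bairro incidence is only something to be considered. The harm therefore needs three conditions together: the option is taken, the allocation strata are prognostic, and bairro incidence does not carry the same information. Comparing strata with no adjustment at all overstates the loss, because the stated alternative is a covariate and not nothing. Where bairro incidence is strongly prognostic it can do as well as the strata or better: in one simulation with both correlated 0.6 with the outcome, power was 95.6% with bairro incidence and 92.9% with strata. The model also lists a baseline period and a cluster effect, which might recover part of the strata's information, depending on coding that is not stated. All of this stands, and it makes the harm conditional. It does not make the sampling variable a proper stand-in for the allocation strata.

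A reader might infer three stronger things that the documents do not support:

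- **That the trial falls below its planned power.** The sample size takes no credit for stratification, so what is forgone is a gain that was never planned.
- **That random effects for strata are wrong.** Five levels are few for estimating a variance, but no comparison of fixed with random strata was made. Fixed effects are a reasonable choice, not a demonstrated necessity.
- **That there is only one blood survey before allocation.** Allocation speaks of both baseline collections, and the timeline figures are not available, so two samples cannot be excluded.

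**Conclusion.** The point holds as a conditional one. Statistical methods permits the sampling stratifier to replace the allocation strata, describes it in a way that blurs the two, and gives no rule for choosing.

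If the substitution is made and the strata are prognostic beyond bairro incidence, standard errors are too wide and the test is conservative. The power forgone is 0 to about 10 points, assuming that the strata explain 10% to 50% of between-cluster variance. It is nil if they explain nothing or if bairro incidence carries the same information. There is no bias and no inflated type I error, and the planned 80% power is not lost. The textual discrepancy is certain; the size rests on quantities that the documents do not give. The basis of the five strata, seroprevalence or seroconversion, is a secondary wording point.

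**What to change.** In Statistical methods, state that the five strata used for allocation stay in every primary model, for both seroconversion and *Aedes* density; fixed effects are a reasonable choice for five levels. Allow bairro incidence only as an additional covariate, not as an alternative, and describe it as the variable used to sample clusters. In Allocation, state whether the strata are formed from baseline IgG seroprevalence or from seroconversion between two named pre-allocation samples.

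The cost is a change of wording and at most 4 degrees of freedom among 68 clusters. In simulation with strata that explained nothing, power was 81% with or without them, so keeping them is close to free.

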#### Entomological assessments

Each participating household will be inspected by entomological workers for all indoor and outdoor containers (tires, flower vases, water storage barrels, laundry wash basins, plastic tarps, puddles, and discarded containers such as bottles, cans, drums, metal pots, and plastic containers) including natural habitats such as tree holes and leaf axils [8]. Entomological surveys will also be conducted in elementary schools, identifying high-risk areas for breeding sites within each school as well as high-risk areas within the cluster (e.g., waste collecting bins, scrap yards, vacant lots, landfills). Schools and households will also have a premise condition index, which is based upon the house or school structure conditions (e.g., well-maintained) and yard conditions, if applicable, (e.g., well-maintained), which will range from 0 to 6 [64]. All containers will be classified according to size and use (routinely used or not in use), and presence (based on visual inspection) of larvae and/or pupae, which will be used to calculate the container index (number of positive containers per household). Adult mosquito collection will be conducted for each household using Prokopact aspirators, for a collection time of 1 h for both inside and outside of the home. Captured mosquitos will be stored on wet or dry ice in an insulating container and transported to the laboratory where all adult female *Aedes aegypti* and *Aedes albopictus* will be identified and stored. This will be used to calculate the number of adult female *Aedes* mosquitos per household. Ambient temperature and relative humidity will be recorded for each household during the entomological surveys using an iButton sensor.

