#### Approach for participant retention

Based on experience in pilot work ranging between 10% [7] to 20% [45] loss to follow-up with 2 visits, we have estimated a 30% rate of attrition in the current study, due to increased length of follow-up (4 follow-up visits). Participation and follow-up will be encouraged by offering at-home visits and the possibility of rescheduling visits when necessary. All data collection milestones will be scheduled in consultation with the local steering committee to determine the best possible time for the community. Advertisement will be made within the community prior the home visits for data collection to inform households of the upcoming visit of the research team. To compensate for losses due to attrition, decreased participation, and potential biological sample losses, we plan a 43% increase in recruitment.

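### The model stated for Aedes density has one time term per yearly survey, although a survey may fall anywhere in a January to May rainy season and visit dates are not balanced by arm

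*Protocol article*

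**What the plan says.** All references are to the protocol article.

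- **Model (Statistical methods).** For Aedes density, "we will use the same approach: a conditional (multilevel) modeling approach (i.e., using mixed effects models) with a Poisson distribution". The seroconversion model described just before it has "random effects for strata, measurement period (baseline, first follow-up, second follow-up), household, and census tract (cluster" as its random terms. Period is the only term for time.
- **Covariates (Statistical methods).** "Additional baseline covariates may be considered for inclusion at the patient and household level (e.g., age, sex, socioeconomic status". On KAP and social capital, "they will be examined as potential effect modifiers/confounders with each outcome". Neither survey date nor month is mentioned.
- **Survey window (Participant timeline; Study setting).** "Following baseline, entomological surveys will occur yearly during the rainy season". The rainy season is given as January to May. The serology surveys are placed five months after the peak of that season; the entomology is tied only to the season.
- **Dates (Approach for participant retention).** Data collection is scheduled with the local steering committee "to determine the best possible time for the community", and visits may be rescheduled. No rule balances visit dates between arms.
- **Weather readings (Entomological assessments).** "Ambient temperature and relative humidity will be recorded for each household during the entomological surveys". No analysis of Aedes density names them.

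**The concern.** A tract surveyed in January and one surveyed in May of the same year share one period effect. If density changes over those months, the change appears as a difference between tracts that the model cannot explain, and a primary outcome loses precision. The listed random effects also include no tract-by-period term. If they are carried over as they stand, date effects that differ between surveys within a tract may not be fully reflected in the reported standard error.

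A second risk arises only if dates differ systematically by arm. Intervention communities are actively engaged and control communities are not, so scheduling could drift apart after allocation. Season would then be mixed with the intervention effect, and nothing in the plan guards against this.

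**Working it through.** **The plan's own figures.** The article gives no sample size, mean count or variance for Aedes density. Its calculation is for seroconversion: risks 0.30 and 0.2115, ICC 0.07, 60 children per cluster, 80% power, significance level 0.05. Taken as two-sided, this gives 381 children per arm before clustering; the design effect is 1 + 59 × 0.07 = 5.13; 381 × 5.13 / 60 = 32.6 clusters per arm, close to the stated 32. Also 60/0.7 rounds up to 86, and 86 × 68 = 5848. These figures hold and are unaffected by this point. What follows is a set of scenarios.

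**Could a round be long?** Each household needs 1 h of collection. At an assumed 1.2 to 2.0 enrolled children per household, 5848 children live in 5848/2.0 = 2,924 to 5848/1.2 = 4,873 households. At an assumed 6 households per team-day, that is about 490 to 810 team-days at full enrolment. The number of teams is not given, so calendar length cannot be derived; weeks to months is plausible.

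**Precision.** Assumptions:
- survey dates uniform over the season and independent between surveys;
- ratio R of highest to lowest density within the season of 1.5, 2 or 3;
- between-tract log variance τ² of 0.1, 0.25 or 0.5;
- within-tract variance 0.03 per survey;
- 34 tracts per arm; k = 1 or 2 follow-up surveys.

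For a steady log-linear change, the variance due to date is s² = (ln R)²/12 = 0.0137, 0.040 and 0.101. For a mid-season peak (half-sine shape), simulation gives 0.0156, 0.045 and 0.114. Leaving date out multiplies the standard error by

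√[(τ² + 0.03/k + s²/k) / (τ² + 0.03/k)].

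Example, R = 2, steady change, τ² = 0.25, k = 1: √(0.32/0.28) = 1.07.

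Range over both shapes and all three τ²:

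| R | k = 1 | k = 2 |
|---|---|---|
| 1.5 | 1% to 6% | 1% to 3% |
| 2 | 4% to 16% | 2% to 9% |
| 3 | 9% to 37% | 5% to 22% |

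With k = 2, 15 of the 18 scenarios lie below 10%.

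**Power illustration.** Take τ² = 0.25, k = 1 and a rate ratio of 0.705, borrowed from the 29.5% reduction assumed for serology. With season fully adjusted, SE = √(2/34 × 0.28) = 0.128 and power is 78%. Unadjusted, power is 76%, 71% to 72%, and 63% to 65% for R = 1.5, 2 and 3.

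**Bias, if dates differ by arm.** The season has 151 days, or 21.6 weeks. Under a steady change, a difference of w weeks in mean survey date gives a false ratio of R^(w/21.6), or its inverse:
- w = 2: 1.04, 1.07, 1.11 for R = 1.5, 2, 3;
- w = 4: 1.08, 1.14, 1.23.

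**Chance imbalance.** With 34 tracts per arm and uniform dates, the difference in mean date has SD 151/√12 × √(2/34) = 10.6 days. This is part of the variance above; it is not bias.

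**The case against.** The strongest reply is that this is a journal article without its analysis plan. The covariate list is open, nothing in it excludes date or weather, and visit order may be set in the operating procedures that the article says will cover all trial procedures. In part this stands: the final covariate set can be settled later. But the article does state the time term, and that term does not deal with timing within a season. Balance of visit dates is also a field matter that no later analysis plan can restore once the visits are done.

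A reader might infer stronger claims that the document does not support:

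- *The Aedes model is restricted to child characteristics.* It is not. The covariates are at patient and household level, socioeconomic status is one example, and KAP and social capital are examined for every outcome. None of these, however, captures season.
- *Each community picks its own dates.* The text describes scheduling with a local steering committee. This may mean the timing of whole rounds and not a choice of week by each tract.
- *The temperature and humidity readings were taken to adjust this model, or will go unused.* No purpose is given for them. The spatial analyses foresee unnamed environmental predictors, though of dengue transmission risk and not of Aedes density.
- *Surveys will last five months.* That spread is permitted, not stated. A compact round would shrink every figure above.
- *The comparison between arms is seasonally biased.* Nothing shows that dates will differ by arm. With a mid-season peak, a small shift in mean date would largely cancel.

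**Conclusion.** The point holds as a worthwhile, inexpensive improvement to a primary analysis and its field schedule; it is not a demonstrated bias. The stated approach has no term for timing within a survey year, and the field plan as described does not balance timing by arm. If rounds are spread over the season and density varies 1.5- to 3-fold, the likely cost is a standard error larger by about 1% to 37%, mostly under 10% with two follow-up surveys. A false rate ratio of about 1.04 to 1.11 requires both a systematic two-week difference between arms and a steady seasonal trend. All these sizes rest on assumed seasonal range, tract variance and date spread, because the article gives no Aedes data from which to set them.

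**What to change.** 1. **Field schedule.** In every post-allocation entomological survey, visit intervention and control tracts of the same randomization stratum in the same weeks. Record the visit dates and report their distribution by arm.
2. **Model.** Prespecify survey date as a covariate for Aedes density, as a smooth or monthly term within year, in addition to the period effect. The recorded household temperature and humidity can be optional further covariates; the benefit of adding them was not quantified here.

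Cost: communities have somewhat less choice of visit week, and the model gains a few terms. No new measurements are needed, provided the survey forms carry the visit date. The scheduling step matters most, because it protects the comparison even if the seasonal term is misspecified.
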